## Abstract

**Background:**

To increase cardiovascular disease prevention efforts, worksite interventions can promote healthy food choices, facilitate health education, increase physical activity and provide social support. This pioneer study will measure the effectiveness of a cafeteria and a behavioral intervention on cardio-metabolic risk in a worksite in Nepal.

**Methods:**

The Nepal Pioneer Worksite Intervention Study is a two-step intervention study conducted in Dhulikhel Hospital in eastern Nepal. In the first step, we will assess the effectiveness of a 6-month cafeteria intervention on cardio-metabolic risk using a pre-post design. In the second step, we will conduct a 6-month, open-masked, two-arm randomized trial by allocating half of the participants to an individual behavioral intervention based on the ‘diabetes prevention program’ for the prevention of cardio-metabolic risk. We will recruit 366 full time employees with elevated blood pressure, fasting blood sugar, or glycosylated haemoglobin (HbA1c). At baseline, we will measure their demographic variables, lifestyle factors, anthropometry, fasting blood sugar, HbA1c,and lipid profiles. We will measure cardio-metabolic outcomes at 6 months, 12 months, and 18 months.

At 12 months, we will compare the proportion of participants who have attained two or more cardio-metabolic risk factor reduction goals (HbA1_c_ decrease ≥0.5%; systolic blood pressure decrease ≥5 mmHg; or triglycerides decrease ≥10 mg/dL) during the cafeteria intervention period and the control period using generalized estimating equations. At 18 months, we will compare the proportion from the ‘cafeteria only arm’ to the ‘cafeteria and behavior arm’ for the same outcome using a chi-square test.

**Discussion:**

This pioneer study will estimate the effect of environmental-level changes on lowering cardio-metabolic risks; and added benefit of an individual-level dietary intervention. If the study demonstrates a significant effect, a scaled up approach could produce an important reduction in cardiovascular disease burden through environmental and individual level prevention programs in Nepal and similar worksites worldwide.

**Trial registration:**

The trial was retrospectively registered on clincaltrials.gov (Identification Member: NCT03447340; Date of Registration: February 27, 2018).

**Electronic supplementary material:**

The online version of this article (10.1186/s12872-019-1025-3) contains supplementary material, which is available to authorized users.

## Background

The burden of non-communicable diseases (NCDs), such as cardiovascular disease (CVD), diabetes, cancer, and chronic obstructive pulmonary disease (COPD), are on the rise in low- and middle- income countries [1]. CVD is the leading cause of morbidity, mortality, and disability in South Asia, where 20% of the world’s population resides [2].

Sedentary lifestyle, poor diet, and excessive body weight are reported to have a large effect on the risk of developing NCD’s [3, 4]. Lifestyle interventions addressing diet and exercise have reduced cardiovascular risk [5, 6]. Despite the evidence supporting the use of lifestyle interventions to prevent hypertension and diabetes and to improve glucose tolerance, their translation into real world settings has been challenging. Worksites provide unique opportunities for health promotion and disease prevention programs since many people spend a majority of their time at work, and they allow access to large segments of the population. Worksites also provide an infrastructure and natural environment for social support. Worksite-based health programs have shown positive impacts on employee health [7, 8], and they have led to significant improvements in cardiovascular risk factor profiles [9, 10]. Worksite interventions encompassing environmental changes (i.e. low-cost healthy food options), places for physical activity (i.e. fitness centers or gyms), and group-based health education classes, have been highlighted as components of successful worksite interventions [11, 12]. However, much of these evidences come from high income countries and there is limited studies from low income setting.

Thus, we planned a study that will measure the effectiveness of a cafeteria-based intervention (adding healthy foods and reducing or removing unhealthy foods), combined with a behavioral intervention, on cardio-metabolic risk among employees of a hospital based in Nepal, by evaluating the change in number of individuals reaching two or more cardio-metabolic risk goals, specifically reductions in blood pressure, triglycerides, and glycosylated hemoglobin (HbA1c).

If proven effective, the cafeteria, behavioral or both interventions can be scaled up in the worksites in Nepal. According to the Labor Force Survey 2008, the labor force comprises of 12 million people with a participation rate of 83.4%. An estimated 3 million adults work in formal employment including legislators, professionals, technicians, clerks, service workers, market agriculture, craft and trade, machine operators and armed forces [13]. Hence, the worksite based health promotion programs have potential to impact on the population health at large in Nepal.

## Methods

### Study design

The Nepal Pioneer Worksite Intervention Study is a two stage intervention study. In the first stage, we will use a pre-post design to assess how a cafeteria intervention that provides a healthier diet, affects cardio-metabolic risk. In the second step, we will conduct an unmasked two-arm randomized trial by allocating half of the participants to continue the cafeteria intervention in addition to a behavioral (CB) intervention for the prevention of cardio-metabolic risk, while the other half of participants will receive the cafeteria-only (CO) intervention. (Fig. 1) The study protocol has been approved by the institutional review committee at Harvard T.H. Chan School of Public Health, Nepal Health Research Council, and Kathmandu University School of Medical Sciences. The study has been retrospectively registered in clinicaltrials.gov (Identification Member: NCT03447340) on February 27, 2018.

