#### Screening

The RAs will conduct a 2 phased screening process to identify eligible participants. In the first screening, the RAs will screen participants by measuring blood pressure and administering a questionnaire along with measures that it make it possible to calculate the Indian Diabetes Risk Score (IDRS) [14]. The IDRS takes age, abdominal obesity, self-reported physical activity, and family history of diabetes into account. The IDRS score ranges from 0 to 100, with a high number indicating higher risk. The IRDS has been considered a reliable instrument to screen the risk of diabetes in Asian-Indian populations [14]. An IDRS of 30 or more has been shown to have 95% sensitivity and 45% specificity to detect prediabetes using fasting blood sugar criteria (100–120 mg/dL); and 87% sensitivity and 47% specificity using HbA1c criteria (HbA1c 5.7–6.5%) in an analysis of 560 free residents of Dhulikhel (Unpublished).

Blood pressure will be measured in the right arm of seated participants, after a five- minute rest period. Three measurements of systolic and diastolic blood pressure will be taken using a Microlife automatic blood pressure measuring device. The mean of three blood pressure measurements will be used. Participants with systolic blood pressure of ≥120 mmHg or diastolic pressure ≥ 80 mmHg will be invited to participate regardless of their IDRS score. In the second screening, the participants scoring 30 or more on IDRS will be asked to provide a blood sample to measure HbA1c and fasting blood glucose. The individuals with HbA1c between 5.7 to 6.4% or fasting blood sugar of ≥100 mg/dL will be invited to participate. All eligible individuals that provided informed consent will be enrolled. No compensation or reimbursement will be provided to the participants.

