### Primary and secondary outcomes

The primary outcome will be the proportion of individuals reaching two or more of their cardio-metabolic risk goals, reductions in blood pressure, triglycerides, and HbA1c. Participants will be scored on the number of improved risk factors (0–3) as defined by decreases in (1) HbA1c ≥0.5%; (2) systolic blood pressure ≥ 5 mmHg; or (3) plasma triglycerides ≥10 mg/dl. These outcomes were selected because blood pressure, HbA1c, and triglycerides are commonly measured in clinical settings. This makes their use clinically appropriate and translatable, especially since other CVD risk scores such as the Framingham Risk Score, do not perform well in South Asian populations [25]. Moreover, the composite outcome allows for individuals to reduce different factors based on their variable risk profiles at baseline. For example, an individual with a baseline systolic blood pressure of 120 mmHg many not reduce this risk factor by as much as 5 mmHg, but may succeed in reducing HbA1c or triglycerides. The secondary outcomes are absolute changes in HbA1c, systolic blood pressure, diastolic blood pressure, and triglycerides individually.

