### Data management

We have taken four robust provisions to ensure data quality. First, the electronic questionnaire will be closed only if the data collection is complete to avoid partial or missing values. The data will be cleaned and checked every month. The answer fields for all integer variables will be constrained to ensure entry of only valid numbers. Second, RAs will receive intensive training on data collection and ethical considerations. Third, the site investigator will supervise the RAs on a day-to-day basis. Fourth, the principal investigators will hold weekly meetings with site investigators, and if required, with the RAs, to discuss the course of the intervention and to address any issues.

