### Minimization of contamination

The risk and level of contamination during the randomized study phase for the behavioral intervention will be monitored at the participant level. The participants will be instructed not to share information about the study and not to provide any support to people in their worksite, other than their classmates. The behavioral classes will be conducted in a separate building outside of their workspace to ensure privacy. Further, we will measure possible contamination by asking if the participants have received any information / advice regarding diet and lifestyle changes from any of their peers and if they did, collect the name and contact information of the peer. If the contamination is found to be significant, we will make adjustments by adding the contamination as a variable in the final model while estimating the effect in secondary analysis.

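### The CO versus CB stage is declared unmasked without limit, and nothing keeps the person who measures month-18 blood pressure from knowing the arm, so observer bias can enter the primary endpoint

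*Protocol article*

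**What the plan says.** Study design: "we will conduct an unmasked two-arm randomized trial". The abstract has "we will conduct a 6-month, open-masked, two-arm randomized trial", a term that does not show who, if anyone, is masked. The only blinding described is in the Laboratory section, where laboratory personnel are blinded to the 5% of samples sent in duplicate.

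Primary and secondary outcomes: "The primary outcome will be the proportion of individuals reaching two or more of their cardio-metabolic risk goals". The blood pressure goal is a fall in "systolic blood pressure ≥ 5 mmHg". The other two goals are laboratory values: HbA1c (fall of at least 0.5%) and triglycerides (fall of at least 10 mg/dL).

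Blood pressure procedure is given only under Screening. There, "the RAs will screen participants by measuring blood pressure" names research assistants (RAs) as the measurers, and "Three measurements of systolic and diastolic blood pressure will be taken using a Microlife automatic blood pressure measuring device" gives the device. The participant is seated, the right arm is used after five minutes of rest, and the mean of the three readings counts. The Follow up section repeats the measurement at 6, 12 and 18 months without naming a role.

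Three other sections bear on who may learn the arm:
- Minimization of contamination: "we will measure possible contamination by asking if the participants have received any information / advice", again with no role named and no place in the visit.
- Data management: RAs may join the weekly meetings if required, "to discuss the course of the intervention and to address any issues", and the site investigator supervises them daily.
- Intervention fidelity: a site investigator also supervises delivery of the intervention, and class knowledge is tested before and after.

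**The concern.** People who attend group classes cannot be masked. The person who takes their blood pressure can be, but the plan calls the whole stage unmasked and draws no such line. Someone who knows the arm can influence a reading without misreading the display, for example through conversation, encouragement, or how strictly rest and repeat readings are handled.

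Because success on this component turns on a 5 mmHg cut-off, a small systematic difference between arms moves people across the line. This is the only comparison in the study that randomisation protects. A measurement difference that follows the arm would look like an effect of the classes, and the planned chi-square test could not tell the two apart.

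**Working it through.** **1. The plan's own figures.** Inputs from Sample size and power: CO success 0.315, relative risk 1.5, 80% power, 5% level (taken as two-sided), 5% loss, N = 320.
- CB success = 0.315 × 1.5 = 0.4725; planned difference = 0.1575, or 15.75 points.
- Two-proportion formula without continuity correction: p̄ = 0.39375, n = [1.960·√(2·p̄·(1−p̄)) + 0.842·√(0.315·0.685 + 0.4725·0.5275)]² / 0.1575² = 149.9, so 150 per arm and 300 in total. 300/0.95 = 316, close to the stated 320.
- With 152 analysed per arm (160 × 0.95), power is 80.6%.
- Table 3, systolic pressure, independent samples: 13.32·√(2/152)·(1.96 + 0.84) = 4.28 mmHg, against the stated 4.3.

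The stated figures reproduce, and this point disputes none of them.

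**2. Model for illustration.** The documents give no size for observer bias, so it is assumed.
- Changes are normal with SD = s·√(2(1−ρ)), where s is the Table 3 SD (13.32 mmHg, 82.47 mg/dL, 0.38%) and ρ is the assumed correlation between a person's two measurements, 0.5 to 0.7.
- The three goals are independent.
- The classes have no true effect.
- Every CB reading is shifted by a constant false fall of b mmHg.

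Let S, T and H be the probabilities of the systolic, triglyceride and HbA1c goals. Then

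P(two or more) = T·H + S·(T + H − 2·T·H).

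**3. No average change in either arm, ρ = 0.5.** S = P(Z > 5/13.32) = 0.354, T = P(Z > 10/82.47) = 0.452, H = P(Z > 0.5/0.38) = 0.094.
- b = 0: 0.206.
- b = 2: S = P(Z > 3/13.32) = 0.411, giving 0.232 (+2.6 points).
- b = 3: S = 0.440, giving 0.245 (+4.0 points).

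At ρ = 0.7 the base is 0.159, and b = 2 gives 0.191 (+3.2 points).

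**4. Anchored on the plan's CO rate of 0.315.** All three goals are moved by the same number of SDs until P(two or more) = 0.315. At ρ = 0.5 this gives S = 0.446, T = 0.547, H = 0.141. With b = 2, S = 0.506 and the gain is (0.506 − 0.446) × 0.534 = 0.032. The last column is the two-sided rejection probability at a nominal 5% (Wald approximation, 152 per arm).

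| False shift in CB | Added success, ρ 0.5 to 0.7 | Rejection probability |
|---|---|---|
| 1 mmHg | 1.6 to 2.2 points | 6 to 7% |
| 2 mmHg | 3.2 to 4.4 points | 9 to 13% |
| 3 mmHg | 4.8 to 6.6 points | 14 to 23% |
| 5 mmHg | 7.9 to 10.8 points | 31 to 50% |

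**5. How much the second goal protects.** Success without the systolic goal needs both laboratory goals: T·H·(1−S). In step 3 at ρ = 0.5 this is 0.452 × 0.094 × 0.646 = 0.027 of 0.206, so about 87% of modelled successes include the systolic goal. At ρ = 0.7 it is about 91%.

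**The case against.** The strongest defence is that the measurement is hard to bias. The device is automatic, and position, arm, rest and number of readings are fixed, with the mean used. If the Screening section is read as naming the month-18 measurers, its procedure must carry over as well. What remains is departure from procedure and encouragement. Systolic pressure alone also never makes a success. All this stands and limits the bias. The second goal protects less than it seems to, because the HbA1c goal is rarely met in the model and most successes therefore run through systolic pressure.

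A second defence is that visit order, staff assignment and custody of the allocation list usually sit in a fuller protocol. That is fair for those details taken alone. But the unmasked status of the stage is a stated design choice, and as written it covers everyone.

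Some stronger readings are tempting, but the documents do not support them:
- A reader might infer that the RAs who take month-18 blood pressure also ask about contamination and so learn the arm first. Both sections say only that the study team will do this. That RAs measure blood pressure at follow-up is a fair inference, but it is not stated.
- The meetings RAs may attend are listed as a data-quality measure. Nothing says that individual allocations are discussed there.
- A reader might add that a dietitian both teaches the classes and takes the diet recalls. The text does not say it is the same person, and diet is neither a primary nor a secondary outcome.

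**Conclusion.** The plan leaves an avoidable route for assessor bias into the primary endpoint of its only randomised comparison. It does not show that bias will occur, and its size is unknown. Under the assumptions above (a constant 2 mmHg false shift, independent goals, no true effect, CO success of 31.5%), success in CB would rise by about 3 to 4 points against a planned 15.75. The chance of a false positive would rise from 5% to about 9 to 13%. A shift of 3 mmHg or more would matter more, but nothing in the documents supports a particular value. The case for acting is that the remedy is cheap. It is a change that should be made, with medium confidence.

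**What to change.** In Study design, replace the blanket description with one by role: participants and class facilitators are unmasked; the staff who measure month-18 blood pressure and the laboratory staff are masked to arm. Use the same wording in the abstract. Then add:
- At month 18, blood pressure and the blood draw come before any contamination or knowledge question, and participants are asked not to mention classes until both are done.
- The allocation list is held away from those who measure outcomes, and also from the site investigator who supervises them day to day.
- Where existing staffing allows, RAs with no role in the classes take the month-18 blood pressure. The article gives no RA numbers or division of tasks, so the sponsor must confirm that this is feasible.

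No measurement, analysis or sample size changes. The cost is some scheduling effort. Some accidental unmasking will still occur, and bias from participants knowing their own arm remains.

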**Fig. 1 Fig1:**
[figure not shown]
Planned flow of participants through the Nepal Pioneer Worksite Intervention Trial

### Study setting

The study will be conducted at Dhulikhel Hospital - Kathmandu University Hospital (DH-KUH) in central Nepal. Dhulikhel Hospital is an independently owned, not-for-profit institution which was conceived and supported by the Dhulikhel community. The hospital has approximately1040 employees and four cafeterias that are in operation 16 hours a day. There are no gyms or other facilities to help physical activity onsite. The hospital does not currently offer any wellness programs for the prevention of cardiometabolic diseases.

### Recruitment

We will conduct a 20-min information session in all of the hospital departments. Employees will be invited to attend sessions by flyers posted around the hospital and through announcements in department meetings. During the information session, we will explain the purpose and the expectations of the study. We will explain the ethical considerations, emphasizing the importance of protecting participant’s privacy during research-related interactions and outcomes, the volunteer nature of the study, the option to drop out of the study at any time, and we will establish that there will not be any coercion from supervisors to participate in the study. After the information session, research assistants (RAs) will set up appointments for eligibility screening among interested participants.

The inclusion criteria are: (a) adults 18 years or older; (b) full time employees of DH-KUH; with (c) systolic blood pressure of ≥120 mmHg or diastolic pressure ≥ 80 mmHg; or HbA1c of 5.7 to 6.4%, or fasting blood sugar of ≥100 mg/dL. The exclusion criteria of the study are: (a) pregnant women, since dietary habits may change during pregnancy, (b) taking diabetes medication, or (c) taking hypertension medication. Those employees who are taking medication receive free drugs and lifestyle counselling in the hospital’s diabetes and hypertension clinic. The RA will obtain written informed consent in a private room for those individuals who are deemed eligible to participate in the study. A short oral consent process will be utilized for participants who cannot read the consent form. This will entail presenting all of the elements of the consent form verbally to the participant, in the presence of a witness. The witness will be required to sign a document stating the consent form has been verbally presented to the participant.

### Data collection

The schedule of enrollment and assessment is presented in Table 1. At baseline, we will measure demographics, anthropometry, blood pressure, lifestyle, blood sugar and lipid profile. After 6 months of control period (without any intervention), we will measure the anthropometry, lifestyle, blood sugar and lipid profile. We will implement the cafeteria intervention for 6 months and re-measure the anthropometry, lifestyle, blood sugar and lipid profile at 12 months. Then, we will randomize half of the participants to continue the cafeteria intervention in addition to a behavioral intervention for the prevention of cardio-metabolic risk, while the other half of participants will receive the cafeteria-only intervention. We measure the anthropometry, lifestyle, blood sugar and lipid profile at 18 months.

**Table 1 Tab1:** The schedule of enrollment and assessments for the Nepal Pioneer Worksite Intervention Trial

	Screening Month 1	Baseline Month 1–2	Follow up - 1 Month 6	Follow up- 2 Month 12	Follow up- 3 Month 18
Indian Diabetes risk score questions (age, sex, family history of diabetes self-report moderate physical activity)	X				
Demographic information (age, sex, ethnicity, education, income, religion, marital status)		X			
Anthropometry					
Height		X			
Weight		X	X	X	X
Waist circumference	X	X	X	X	X
Hip circumference		X	X	X	X
Blood Pressure	X	X	X	X	X
Lifestyle factors					
Two 24 Hour Dietary recall		X	X	X	X
Global physical activity questionnaire		X	X	X	X
Smoking and Drinking habits		X		X	
Laboratory					
Glycated hemoglobin	X	X	X	X	X
Fasting Blood Sugar	X	X	X	X	X
High density lipoprotein cholesterol		X	X	X	X
Low density lipoprotein cholesterol		X	X	X	X
Triglycerides		X	X	X	X
Total Cholesterol		X	X	X	X

#### Screening

The RAs will conduct a 2 phased screening process to identify eligible participants. In the first screening, the RAs will screen participants by measuring blood pressure and administering a questionnaire along with measures that it make it possible to calculate the Indian Diabetes Risk Score (IDRS) [14]. The IDRS takes age, abdominal obesity, self-reported physical activity, and family history of diabetes into account. The IDRS score ranges from 0 to 100, with a high number indicating higher risk. The IRDS has been considered a reliable instrument to screen the risk of diabetes in Asian-Indian populations [14]. An IDRS of 30 or more has been shown to have 95% sensitivity and 45% specificity to detect prediabetes using fasting blood sugar criteria (100–120 mg/dL); and 87% sensitivity and 47% specificity using HbA1c criteria (HbA1c 5.7–6.5%) in an analysis of 560 free residents of Dhulikhel (Unpublished).

Blood pressure will be measured in the right arm of seated participants, after a five- minute rest period. Three measurements of systolic and diastolic blood pressure will be taken using a Microlife automatic blood pressure measuring device. The mean of three blood pressure measurements will be used. Participants with systolic blood pressure of ≥120 mmHg or diastolic pressure ≥ 80 mmHg will be invited to participate regardless of their IDRS score. In the second screening, the participants scoring 30 or more on IDRS will be asked to provide a blood sample to measure HbA1c and fasting blood glucose. The individuals with HbA1c between 5.7 to 6.4% or fasting blood sugar of ≥100 mg/dL will be invited to participate. All eligible individuals that provided informed consent will be enrolled. No compensation or reimbursement will be provided to the participants.

